### Outcome measurements

#### Primary outcomes

Hospital Anxiety and Depression Scale (HADS) [46]. There are 14 items, including 7 items on anxiety and 7 items on depression. A score of 0–7 means the participant is asymptomatic, 8–10 is suspicious, and 11–21 means symptomatic. Cronbach α coefficients of the total scale, as well as the anxiety and depression subscales are 0.88, 0.81 and 0.81, respectively [49].

Memorial Symptom Assessment Scale–Short Form (MSAS-SF), which is used to evaluate the characteristics of physical and psychological symptoms of cancer patients [50]. There are 32 items consisting of 2 subscales: physical symptoms and psychological symptoms. The incidence and frequency of each symptom will be evaluated. The Cronbach's alpha coefficient ranged from 0.84 to 0.91 [51].

#### Secondary outcomes

Functional Assessment of Cancer Therapy–General (FACT-G). It is a general scale used to evaluate the cancer patients' quality of life. There are 27-item consisting of 4 subscales: physical, social, emotional and functional wellbeing (total score of 0–108; higher scores = better QoL), Cronbach α is 0. 88, 0. 82, 0. 87, 0. 83,respectively [52].

Coping, which is measured with the mini-Mental Adjustment to Cancer Scale (mini-MAC) [53], a 29-item scale yielding 5 factors: Fighting Spirit, Helplessness/Hopelessness, Anxious Preoccupation, Fatalism, and Cognitive Avoidance. Items are responded to on a 4-point scale ranging from ‘definitely does not apply’ to ‘definitely does apply’.

Benefit Finding of Cancer Patients Scale(BFS). The scale was adapted by Weaver et al. [54], which was employed in prior studies of gynecological cancer patients [55]. Benefits included both interpersonal and intrapersonal changes from cancer. Higher scores indicated perceiving more benefits from cancer.

#### Other outcomes

Demographics and clinical variables. The information will be collected for each patient, including age, sex, marital status, educational level, occupation, work status, level of income, diagnosis, stage of disease, and treatment type.

WeChat usage data, which is used to evaluate the usage of WeChat official account by the participant, such as the frequency of login, browsing time.

### Data collection

The patients will be identifed by a unique study inclusion number and by the frst initial of their surname and of their given name. Baseline data will be collected face-to-face immediately after the patients signing the informed consent. Test 1 will be performed immediately after the intervention, test 2 and test 3 will be performed 3 months and 6 months after the intervention, respectively. The "questionnaire star" app on the WeChat platform will be used during test 1, test 2 and test 3 to send online electronic questionnaire to each participant. The questionnaires included HADS, FACT-G, MSAS-SF, mini-MAC, BFS, socio-demographics, and clinical data.

### Statistical analysis

All data were analyzed using the Statistical Package for Social Sciences 22.0(SPSS Inc., Chicago, IL, USA). Two researchers will carry out data analyses.Participants’ characteristics and outcome scores were summarized using means ± standard deviation (SD) or medians [interquartile ranges (IQR)] for continuous variables or frequencies (percentages) for categorical variables. Baseline characteristics and outcomes were compared using independent samples t-test or Mann–Whitney U test from continuous variables and chi-squared test for categorical variables between the intervention and control group. *p* values < 0.05 were considered statistically significant. All analyses will be conducted on an intention-to-treat basis.

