### Study design

#### Trial design

A single-blinded, randomized, controlled, parallel group pre-test, and repeated post-test design will be conducted to investigate the effect of WeChat-based Cognitive behavioral therapy for Chinese gynecological cancer survivors.

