##### Drop-out criteria

(1) the disease progressed to a great extent during the intervention (tumor recurrence or metastasis); and (2) Other forms of psychotherapy are received during the study.

Sample size will be estimated based on previous research with a medium to small effect size [44]. With a power of 0.90, an alpha set at 0.05, and an effect size of 0.47 for the primary outcome of FACT-G scores, each group will be 29 women [21]. We estimate a 30% attrition rate based on an attrition rate of 28.8% in previous research [45]. A minimum of 76 women (38 in each group) are required.

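### The only between-group tests named are unadjusted and cross-sectional, so they use neither the baseline score nor the repeated post-tests that the design collects

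*Protocol article*

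**What the plan says.** All references are to the protocol article. Under Trial design it describes a "parallel group pre-test, and repeated post-test design". The Abstract and Recruitment sections fix four measurement times: before randomisation, at the end of the intervention, and 3 and 6 months later (tests 1 to 3). The Aims section frames its hypotheses over these times.

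The Statistical analysis section first covers descriptive summaries. It then says: "Baseline characteristics and outcomes were compared using independent samples t-test", or Mann-Whitney for continuous variables and chi-squared for categorical ones, between the two arms, with p below 0.05 as the threshold. It names no baseline covariate, no visit term and no main time point. It closes with: "All analyses will be conducted on an intention-to-treat basis". The section on Validity and reliability then describes the analysis method as appropriate.

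The sample size paragraph, placed under Drop-out criteria, states "With a power of 0.90, an alpha set at 0.05, and an effect size of 0.47 for the primary outcome of FACT-G scores", then "each group will be 29 women" and 38 per group after attrition. On attrition it says: "We estimate a 30% attrition rate based on an attrition rate of 28.8% in previous research". The criteria themselves are disease progression during the intervention and receipt of other psychotherapy during the study.

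**The concern.** The article goes beyond leaving the method to another document: it names a family of tests and then defends it. Those tests do not match the data structure. A two-sample comparison of raw scores ignores the same woman's baseline score, which usually explains part of the variation at follow-up. Applied visit by visit, it also ignores the fact that tests 1 to 3 come from the same women.

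What is at stake is mainly precision. With 38 women per arm and 30% expected loss, the trial has little information to spare, and the baseline and repeated scores are already being collected. A second issue is fit with the intention-to-treat statement. A two-sample test, unless paired with some method for missing scores, can use only the women observed, and the article expects a substantial share not to be.

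**Working it through.** **1. Inputs.** From the article: alpha 0.05 (sidedness not stated; two-sided taken here), power 0.90, effect size 0.47 (read as a standardised mean difference), 29 per group before attrition, 38 randomised per group, 30% attrition, three post-tests. Expected completers are 0.70 × 38 = 26.6 per arm, taken as n = 26.

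Not in the article, so assumed: correlation r between any two scores of the same woman, the same for every pair (compound symmetry), over the range 0.3 to 0.8. Women are treated as independent.

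**2. The plan's own figure.** For the named t-test, n per group = 2(1.960 + 1.282)² / 0.47² = 95.1, so 96. The stated 29 does not reproduce; at 29 per group the two-sided t-test has 42% power. The 38 per group equals 29 × 1.3 = 37.7 rounded up, whereas 29 / 0.7 = 41.4 would give 42. That is a separate sample-size problem. It matters here because it shows that 90% power cannot be taken as the starting point.

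**3. Unadjusted test at one visit.** Noncentrality = 0.47 × √(26/2) = 1.69 on 50 degrees of freedom. Power is 38%.

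**4. Baseline-adjusted, one visit.** Adjustment multiplies the variance by 1 − r², so the effective standardised difference is 0.47 / √(1 − r²).

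**5. Baseline-adjusted average of tests 1 to 3.** The variance factor is (1 + 2r)/3 − r². This also assumes the same treatment effect at all three visits.

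Power at 26 per arm (exact t, two-sided 0.05):

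| r (assumed) | Factor, one visit | Power, one visit | Factor, three-visit average | Power, average |
|---|---|---|---|---|
| 0.3 | 0.910 | 41% | 0.443 | 70% |
| 0.5 | 0.750 | 48% | 0.417 | 73% |
| 0.6 | 0.640 | 55% | 0.373 | 78% |
| 0.7 | 0.510 | 64% | 0.310 | 85% |
| 0.8 | 0.360 | 79% | 0.227 | 94% |

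The average passes 90% at r of about 0.76. The single visit does not reach it anywhere in the range.

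**6. Cross-check with partial follow-up.** Take a longitudinal model with 38 randomised per arm, assumed cumulative loss of 10%, 20% and 30% at tests 1, 2 and 3, and a normal approximation. The contrast at test 3 has 44%, 52%, 69% and 84% power for r = 0.3, 0.5, 0.7 and 0.8. The unadjusted comparison of 26.6 per arm has 40% by the same approximation. The three-visit average has 80%, 83%, 92% and 98%. The direction agrees. Because women with partial follow-up contribute, the average reaches 90% here at a somewhat lower r, about 0.7.

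**7. Intention to treat.** Set side by side, the article promises intention to treat for every analysis, expects 30% attrition, and lists progression and other psychotherapy as drop-out criteria. It does not say whether scores are still collected from women who meet those criteria. A mixed model uses every score observed and is valid if missingness depends only on observed data. It cannot supply scores that were never collected, and drop-out for recurrence or metastasis is plausibly related to the unobserved scores.

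**The case against.** **The sentence may concern baseline only.** It follows directly after the descriptive summaries and can be read as a balance check on baseline characteristics and baseline scores. This stands as an ambiguity, so it is not established that the t-test is the planned efficacy analysis. It does not clear the text, though. On that reading the only tests named compare randomised arms before treatment, where any difference is due to chance, while the Validity and reliability section endorses the method. The sentence needs rewording on either reading.

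**Stronger readings the text does not support.** A reader might infer that the tests are per-visit complete-case comparisons, or that the choice between t-test and Mann-Whitney will follow sight of the outcome data. The article says neither; it gives no missing-data method and no selection rule, and both are commonly left to an analysis plan. A reader might also infer that a mixed model would by itself deliver the promised intention-to-treat analysis. It would not: it rests on missing at random, and women with no post-test contribute nothing to a model with baseline as covariate.

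**The large gains belong to one contrast.** The 70–94% is for the three-visit average under a constant effect and compound symmetry. If the sponsor wants the effect at one visit, the relevant figure is 41–79%, and at r = 0.3 the gain over 38% is only about 3 points. This stands.

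**The basis is borrowed.** The 0.47 is for FACT-G, called primary in the sample size paragraph but listed as secondary under Outcome measurements, where HADS and MSAS-SF are primary. The intervention arm is also split into three interacting WeChat groups of 12–13. Any positive correlation within those groups would make all these powers optimistic. Both points stand, so the figures are illustrative.

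**Inefficient is not invalid.** An unadjusted comparison of randomised arms with complete data is unbiased. This also stands: the core of the point is lost precision and a poor fit to the design.

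**Conclusion.** The point holds in a limited form. The between-group tests the article names use neither the baseline score nor the repeated post-tests that its design collects, and the sentence naming them is unclear about whether follow-up outcomes are covered. Baseline adjustment gains precision for any positive correlation. Its size depends on a correlation the documents do not give and on the contrast chosen: from 38% power to 41–79% for one visit, or to 70–94% for the three-visit average, at 26 per arm, an effect of 0.47 and r from 0.3 to 0.8.

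The change does not repair the sample size: a single-visit contrast stays below the stated 90%, and the average reaches it only at high r. Nor does it settle intention to treat, which depends on how the drop-out criteria and expected attrition are handled.

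**What to change.** In the Statistical analysis section, replace the sentence with a linear mixed model for each continuous outcome, including all randomised women with post-test data. Fixed effects: baseline score on the same scale, arm, visit and arm-by-visit, with unstructured within-woman covariance. Pre-specify one contrast, either a named visit or the average over tests 1 to 3, reported with its 95% confidence interval, and quote the power that belongs to that contrast. Drop significance tests of baseline characteristics and keep the descriptive table.

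Reconcile the drop-out criteria and the 30% attrition with the intention-to-treat statement: say whether scores are still collected after a criterion is met and how such women enter the analysis. Add a sensitivity analysis for departures from missing at random.

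Cost: the model is a change of wording that the named software (SPSS 22, MIXED procedure) can carry out on data already planned. The downside is some extra modelling work and reliance on missing at random. Reconciling the drop-out criteria may go further than wording if it means continued outcome collection. All of this should be settled before outcome data are seen.

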## Methods/design

### Aims

The objective of this study was to evaluate the effect of CBT based on the WeChat platform on anxiety, depression, and disease-related symptoms of patients with gynecological malignant tumors in the rehabilitation stage, thereby establishing an intervention model to improve the patient’s coping ability, benefit finding and quality of life. The study hypothesizes that compared with the control group at baseline, test 1, test 2 and test 3, patients in the intervention group will report statistically significant:The degree of anxiety and depression is decreased;Disease-related symptoms are reduced;Coping ability, benefit finding and quality of life are improved.

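### Two unranked primary instruments at three follow-up visits share a flat p < 0.05, and the sample-size paragraph calls a third instrument primary, so the 5% level does not protect a primary claim resting on any one result

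*Protocol article*

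**What the plan says.** - **Primary outcomes.** Two instruments stand under this heading with no ranking. For HADS: "There are 14 items, including 7 items on anxiety and 7 items on depression". For MSAS-SF: "There are 32 items consisting of 2 subscales: physical symptoms and psychological symptoms". Reliability is given for the HADS total as well as for each subscale. The article does not say whether totals or subscales are the primary variables.
- **Aims.** Significant benefit is hypothesised "compared with the control group at baseline, test 1, test 2 and test 3", for anxiety and depression, for symptoms, and for coping, benefit finding and quality of life. No order or success rule is attached.
- **Abstract, Recruitment, Table 1 and Data collection.** There are three assessments after the intervention: immediately, at 3 months and at 6 months. None is called primary.
- **Statistical analysis.** The only inferential methods given are two-group comparisons (t-test or Mann–Whitney, and chi-squared), with one threshold: "values < 0.05 were considered statistically significant".
- **Sample-size paragraph (under Drop-out criteria).** "With a power of 0.90, an alpha set at 0.05, and an effect size of 0.47 for the primary outcome of FACT-G scores". The size derived from these inputs, before attrition, is 29 per arm.
- **Secondary outcomes.** FACT-G is listed here, which contradicts the sample-size paragraph.

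**The concern.** The 5% level is the error rate of one test. The plan applies it to each of several primary comparisons and does not say which of them carries the efficacy claim. Whoever writes the report can then choose among instruments, scores and visits after seeing the results and call the chosen comparison primary. The conflict over FACT-G adds a third instrument for which the text offers support.

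What is at stake is the trial's main conclusion. The trial is small (76 women) and intends to offer evidence of effectiveness. If one nominally significant primary result among several is enough, the stated 5% does not describe the chance of a false claim.

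**Working it through.** **Inputs from the protocol article.** Threshold 0.05 per test (Statistical analysis); two primary instruments with two domains each (Primary outcomes); three post-intervention visits (Abstract, Data collection). Baseline is left out of the count because it precedes the intervention.

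**Assumptions.** Tests are two-sided (sidedness is not stated). Success means at least one significant primary result. The correlation *r* between scores and between visits is not given, so it is varied from 0 to 0.8.

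**The plan's own level.** One comparison at 0.05 gives 1 − 0.95 = 5%. The stated level therefore holds only for a single primary test.

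**Independent tests.** The chance of at least one false finding among *k* tests is 1 − 0.95^k:
- k = 2: 1 − 0.95² = 9.75%
- k = 4: 1 − 0.95⁴ = 18.5%
- k = 6: 1 − 0.95⁶ = 26.5%
- k = 12: 1 − 0.95¹² = 46.0%

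**Correlated tests.** Multivariate normal test statistics were simulated under no effect (400,000 draws; any |z| > 1.96). Scores correlate at *r* and visits at *r*; two tests that differ in both correlate at the product.

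| Family | k | r = 0 | r = 0.3 | r = 0.5 | r = 0.8 |
|---|---|---|---|---|---|
| Two totals, one visit | 2 | 9.75% | 9.5% | 9.1% | 7.8% |
| Four subscales, one visit | 4 | 18.5% | 17.3% | 15.6% | 11.3% |
| Two totals, three visits | 6 | 26.5% | 24.7% | 21.9% | 14.9% |
| Four subscales, three visits | 12 | 46.0% | 42.0% | 35.7% | 21.2% |

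The r = 0 column is the exact formula; the others are simulated.

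**False findings that favour the intervention** (z > 1.96 only), from r = 0 to r = 0.8:
- two totals, one visit: about 5% to 4%
- two totals, three visits: about 14% to 7%
- four subscales, three visits: about 26% to 11%

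The matching nominal level is 2.5%.

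**If both instruments had to succeed at one named visit.** The chance that both are falsely significant cannot exceed the chance that either given one is, so it is at most 5%. There is then no inflation.

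**FACT-G as a third candidate.** Three independent totals at one visit give 1 − 0.95³ = 14.3%, against 9.75% for two.

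**The sample-size figure.** It was checked because it carries the only stated alpha. For two means with a standardised difference of 0.47, two-sided 0.05 and power 0.90, n = 2 × (1.960 + 1.282)² / 0.47² = 95.2, or 96 per group, not 29. That discrepancy is a separate matter. What matters here is that the alpha of 0.05 is assigned to one comparison, on an instrument listed as secondary.

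**The case against.** A condensed article often leaves multiplicity rules to a full protocol or SAP, and neither is shown. The Statistical analysis section is silent on adjustment; it does not say there will be none. That stands, so the missing adjustment alone would be a weak finding. The point rests on what the article does fix: two unranked primaries, a flat threshold, and conflicting statements about which outcome is primary. A later rule would have to settle these first.

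The article also states no success rule. The Aims list the hypotheses together, which fits requiring both primaries as well as it fits accepting either. This too stands: the inflation is conditional on any one result being enough. But the both-must-succeed reading is not stated either, and it would still need a named visit and score.

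A reader might infer that all four subscales are tested at all three visits, and that the false-positive risk is therefore 18–46%, or simply 46%. The documents do not support that. They describe the subscales as parts of the instruments, not as separate analyses, and total scores are equally open. The 46% figure needs twelve independent tests, which is implausible for related symptom scores measured repeatedly in the same women. The 18% is not a floor: two totals at one visit give 8–10%.

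**Conclusion.** The concern holds in a conditional form. As written, the plan does not hold the primary claim at 5% if one significant primary result is enough. The two-sided error is about 8–10% for two totals at one visit, 15–26% for two totals at three visits, and 21–46% if four subscales were tested at three visits. Each range runs from correlation 0.8 to independence. The correlations are assumptions, the 12-test family is not stated in the article, and 46% is its upper bound under independence. About half of each rate consists of false results in favour of the intervention.

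Every such reading exceeds 5%, so the conclusion does not depend on which family is chosen. Only a rule requiring both instruments at one named visit would escape it. The contradiction over FACT-G is certain from the text and needs no assumption.

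**What to change.** Before unblinding:
1. Name one primary instrument, score and visit, for example HADS total at test 1, tested at two-sided 0.05.
2. Test MSAS-SF, with its score named, at the same visit only if the first test is significant. Alternatively, use Holm across the two: the smaller p-value against 0.05/2 = 0.025, then the other against 0.05.
3. Make the subscales, tests 2 and 3, and FACT-G secondary, reported as estimates with 95% confidence intervals and without a claim of efficacy.
4. Reconcile the sample-size paragraph with the Primary and Secondary outcomes sections, so that the effect size and alpha refer to the chosen primary outcome.
5. If the primary comparison is to be baseline-adjusted, add that model to the Statistical analysis section, which now contains only unadjusted two-group tests.

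The choice of instrument and visit, and of sequence or Holm, is the sponsor's; what matters is that it is fixed in advance. The cost is a few lines of text and a restated sample-size justification, with no change to visits or data collected. The downside is that fewer results can be claimed as primary evidence.

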### Validity and reliability

The feasibility of this study design is high, and the measurement tools have high effectiveness and reliability. The statistical analysis method is appropriate, which can effectively reduce error. In addition, because the evaluators and data analysts are blinded from the patient group, biases in the evaluation of intervention outcome can be effectively controlled.

## Discussion

Due to the lack of human and material resources in China, cancer patients are often not provided with effective interventions to ensure their physical and mental health. Under China's current medical and health system, it is more and more imperative to develop a time-saving, efficient, and accessible psychological intervention model that is suitable for local communities. The present study will be the first RCT on the use of CBT through WeChat on Chinese patients with gynecological malignant tumors in the rehabilitation stage. This study can provide evidences for the effectiveness of WeChat on supporting the rehabilitation of patients with gynecological malignant tumors.

